### 4 Trial Duration and Schedule

The duration of the trial for each patient is expected to be about 3 months, including two days of intervention (infusion of frozen CP), followed by a follow-up of 3 months. Furthermore viral load is measured daily in nasopharyngeal swabs at day 1, 2, 3, 5, 7, 10, 14, 28 or until hospital discharge within 84 days after randomization.

Patients randomized into the standard arm of the study have the possibility to cross over into the experimental arm of the study starting from day 10 in case of not improving or worsening clinical condition.

Conditions leading to patient withdrawal from the study are detailed in Section 5.5 Criteria for Withdrawal.

Treatment response is assessed continuously until day 28, thereafter weekly until day 56, 70 and finally at day 84. Primary endpoint is the time to clinical improvement by two points on a seven point ordinal scale or live discharge from the hospital.

A recruitment period of approximately 9 months and an overall study duration of approximately 12 months is anticipated. Recruitment of patients starts in the third quarter of 2020.

The study duration of an individual patient is planned to be 3 months.

After finishing all study-relevant procedures, therapy, and follow-up period, the patient is followed in terms of routine care and treated if necessary.

|                                   |                              |
|-----------------------------------|------------------------------|
| Total trial duration:             | 18 months                    |
| Duration of the clinical phase:   | 12 months                    |
| First patient first visit (FPFV): | 3 rd Quarter 2020 |
| Last patient first visit (LPFV):  | 2 nd Quarter 2021 |
| Last patient last visit (LPLV):   | 3 rd Quarter 2021 |
| Trial Report completed:           | 4 th Quarter 2021 |

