## **6.8 Cross Over**

Cross-over into the experimental arm is intended for patients randomized into the standard arm if the following criteria is met:

- Starting from day 10 after randomization
- No improvement or worsening of clinical condition

For cross-over, all inclusion / exclusion criteria (except mechanical ventilation/ECMO) must again be met as specified in Sections 5.3 and 5.4.

The actual possibility for cross-over into the experimental arm is based on discussion with the coordinating investigator on a case-by-case decision.

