### **General comments on clinical laboratory assessments**

**Laboratory safety assessments** (hematology, coagulation and blood chemistry) are measured at each visit until hospital discharge.

**Urinalysis** by dipstick should be performed at screening/baseline and then only if clinically indicated. Microscopic analysis should be performed by the hospital's local laboratory if required.

Any clinically significant abnormal laboratory values should be repeated as clinically indicated and recorded into the eCRF.

**Serum or urine pregnancy test** is performed for pre-menopausal women of childbearing potential within 14 days prior to the start of study treatment and or prior to randomisation. Tests are performed by the hospital's local laboratory. If results are positive the patient is ineligible/must be discontinued from the study. In the event of a suspected pregnancy during the study, the test should be repeated.

**Viral load in nose/throat swabs and antibody titers** will be determined for the last time at the time of discharge within 84 days after randomization.

Serology tests for SARS-CoV-2 virus IgG antibodies and SARS-CoV-2 neutralizing antibodies will be performed by a central laboratory: Zentrum für Infektiologie, Virologie, Universitätsklinikum Heidelberg, [name], 69120 Heidelberg.

Instructions regarding sample collection, storage and shipment will be provided in the laboratory manual.

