# **10 Statistical Considerations**

## **10.1 Study Design**

This is a randomized open-label, multicenter phase-II study in patients with severe SARS-CoV-2 disease subjects

*Randomisation (rf. also to chapter 6.8):*

Randomisation is done either into experimental arm E or into standard arm S in a 1:1 ratio using block randomisation stratified for the factor "patient group", defined by group 1 (patients with hematological malignancies, history of stem cell transplantation and/or active cancer therapy – incl. chemotherapy, radiotherapy, surgery – within the last 24 months or less.), group 2 (drug induced immunosuppression not meeting the criteria of group 1), group 3 (age  $\geq 50$  - 75 years and meeting neither the criteria of group 1 nor group 2 and Lymphopenia  $< 0.8 \times G/I$  and/or D-dimer  $> 1\mu g/mL$  and group 4 (age  $> 75$  years and meeting neither the criteria of group 1 nor group 2).

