## 10.3 Sample Size Calculation

Based on recently published data median time to an improvement defined as two points on a seven point ordinal scale or live discharge from the hospital is assumed to be at day 16 from randomization. This median estimate considers patients who died without an improvement as censored at day 84 (right-censoring), which ensures that those patients are considered as “not improved” over the whole observation period. In our trial, we follow the same analysis strategy as in Cao *et al.*, 2020 who also censored deceased patients at the end of follow-up.

We assume that based on the mechanism of action (neutralizing antibodies) a rapid improvement is induced by fresh frozen plasma from subjects after convalescence of SARS-CoV-2 infection on two days from two different donors with a median time of 10 days (HR=1.6). Assuming exponentially distributed event times, these assumptions correspond to a hazard of  $\lambda_C = 0.043$  for the control arm, while the corresponding hazard in the experimental arm should amount to  $\lambda_E = 0.043 \cdot 1.6 = 0.69$ .

While it is allowed for patients from the control arm to switch to the experimental arm starting at day 10 (see section 6.8), we assume this will not have a major effect on the median time of clinical improvement for these patients, since we expect that plasma infusions will have a larger advantage if given early. While methods for handling patients switching from control to treatment group are available, they are subject to strong and unverifiable assumptions. Hence, we will ignore treatment switch in the primary analysis, representing a treatment policy strategy (see Section 10.2.1), which can be regarded as a conservative approach since switching is only allowed from the control to the experimental arm. However, in supplementary analyses of the primary endpoint, we will consider such a hypothetical scenario in which a treatment effect is estimated for the case that patients would not have switched by means of inverse probability censoring weighting according to Robins & Finkelstein, relying on the assumption that there are no unmeasured confounders influencing the probability to switch, and a rank preserving structural failure time (RPSFT) model, assuming a common treatment effect which remains constant over time, regardless when treatment is initiated.

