Since patients might die before experiencing a clinical improvement or being discharged from the hospital, death will be taken into account via censoring deceased patients at last day of follow-up (day 84). Based on recently published data, the mortality rate is assumed to be about 20% in the control arm. Thus, we expect that the cumulative improvement rate of the control group will not become larger than 0.8. Hence, fewer improvement events are expected during the follow-up of 84 days than under the assumption of an exponential distribution, since the improvement curves will flatten at some point. In case of the control group, the flattening is expected to occur at day 38, since the assumed cumulative improvement rate at day 38 amounts to  $\exp(-\lambda_C \cdot 38) = \exp(-0.043 \cdot 38) \approx 0.8$ . Accordingly, we conservatively assume a follow-up length of 38 days for the sample size calculation to properly estimate the probability of experiencing the event of interest, even though the actual follow-up for each patient will be longer.

To detect the assumed difference between treatment groups using a log-rank test comparing the cumulative improvement curves for the primary endpoint using a significance level of 5% (two-sided) with a power of 80%, a total number of 174 patients is required for the entire trial (87 patients per group) when additionally considering a dropout rate of 5%, meaning that n=164 patients who do not prematurely drop out of the study are required to be enrolled. The required number of events which was calculated using the formula by Schoenfeld, amounts to 142. It is expected that adjusting for the covariate “patient group” in the analysis will lead to an increase in power. Sample size calculation was done conservatively assuming an equally long follow-up period of 38 days for every patient. Sample size calculation was done using RPACT v 2.0.6.

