A supplementary analysis of the primary endpoint will involve the inverse probability censoring weighting (IPCW) approach to estimate a treatment effect in the hypothetical scenario that patients from the control group had not switched to the experimental group . This type of model requires to estimate the probability for a patient to switch to the experimental group based on (time-dependent) covariates, which in our case will be the baseline factor “patient group”, together with the time-varying factors “seven point ordinal scale measuring clinical improvement” and “viral load” over time. It should be noted that this model implicitly assumes that all relevant confounders predicting whether a patient switches from control to treatment have been included into the model, an assumption which is hardly verifiable, especially for such a recently emerged disease about which we currently only have limited understanding, thus being the reason why we did not choose this as the strategy for the primary analysis.

As another supplementary analysis intending to estimate the treatment effect in the hypothetical scenario which assumes that control patients had not switched to the treatment group, a rank preserving structural failure time (RPSFT) model will be fitted . This model assumes a common treatment effect, meaning that the treatment effect is the same for all individuals (with respect to time spent on treatment) regardless of when treatment is received. Since this is another assumption which is hardly verifiable, and because we especially assume that patients will have a larger treatment effect when plasma is given early, we consider this approach as a supplementary analysis only.

Further sensitivity analyses of the primary endpoint include an analysis based on the per protocol population.

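### The IPCW switching model leaves out the oxygenation measures that gate crossover, so the supplementary switch-adjusted hazard ratios may stay confounded

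*Protocol*

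**What the plan says.** Section 10.5.4 plans an IPCW analysis of the effect had no control patient switched. The model must "estimate the probability for a patient to switch to the experimental group based on (time-dependent) covariates, which in our case will be the baseline factor". That factor is patient group. Two time-varying factors follow, the seven point ordinal scale and viral load, and the list ends there. Section 10.5.5 extends IPCW to overall survival and time until discharge.

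Section 6.8 sets the crossover rule: from day 10, with no improvement or with worsening, after a case-by-case discussion with the coordinating investigator. It adds a gate: "For cross-over, all inclusion / exclusion criteria (except mechanical ventilation/ECMO) must again be met as specified in Sections 5.3 and 5.4". Section 5.3 shows what that involves: SaO2 of 94% or less on ambient air or PaO2/FiO2 below 300 mm Hg, haemoglobin of at least 10 g/dl and, in group 3, lymphopenia and/or raised D-dimer.

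Most of these values are collected. Table 1 schedules FiO2, PaO2, oxygen amount and SOFA daily in hospital to day 28. Section 7.1 says of the safety laboratory values ("hematology, coagulation and blood chemistry) are measured at each visit until hospital discharge").

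Section 10.5.4 concedes that IPCW assumes all relevant confounders of switching are included, calls this hardly verifiable, and for that reason keeps the analysis supplementary, beside an RPSFT model.

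**The concern.** IPCW censors a control at the switch and up-weights similar controls who did not switch. It works only if the weights depend on every variable that drives both switching and outcome. Here the protocol writes one likely driver, oxygenation, into its own crossover rule and then leaves it out of a closed covariate list.

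Take two category-4 controls in the same group with the same viral load. One has SaO2 of 90% on ambient air. The other has 95%, with PaO2/FiO2 of 300 or more. The planned model gives them the same switching probability, yet under Section 6.8 the second cannot switch. If the better-oxygenated patient also recovers sooner, the controls who remain are a healthier subset and the weights do not correct for it.

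At stake is one of only two analyses of the no-switch scenario. The other, RPSFT, assumes an effect that does not depend on when plasma is given, which Section 10.5.4 says the authors do not expect.

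**Working it through.** **1. The plan's own figures.** The protocol gives no figure for the IPCW analysis. Its planning figures (Section 10.3) reproduce. The control median "is assumed to be at day 16 from randomization" and the experimental arm is planned "with a median time of 10 days (HR=1.6"; allocation is 1:1, two-sided 5%, power 80%.
- Events (Schoenfeld): 4(1.960 + 0.842)² / (ln 1.6)² = 142.1; stated 142.
- Event probability by day 38: 1 − exp(−38 ln 2/16) = 0.807 for control and 0.928 at HR 1.6; mean 0.868.
- Patients: 142.1 / 0.868 = 163.8, so 164. With 5% dropout, 82 / 0.95 rounds up to 87 per arm, 174 in all.

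None of this depends on the switching model.

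**2. Rule against model.**

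| Element of the Section 6.8 rule | In the IPCW model? |
|---|---|
| No improvement or worsening | Largely, through the ordinal scale |
| Risk group | Yes, patient group |
| SaO2 or PaO2/FiO2 met again | Only as coarsely as the ordinal scale separates oxygen support |
| Haemoglobin met again | No |
| Lymphocytes or D-dimer met again (group 3) | No |
| Case-by-case decision | No |

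**3. When the omission matters.** An omitted variable biases the result only if, given the ordinal score, it predicts both switching and the outcome. The documents quantify neither link, so the size can only be illustrated.

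**4. Illustration with a graded effect on switching.** Assumptions: 60,000 patients per arm; conditional HR 1.6; daily switching on days 10 to 28, with about 28–33% of controls switching; a two-level ordinal score affecting switching and recovery; and an oxygenation severity marker X. Patient group, viral load and deaths were not simulated, so the planned weights use the ordinal score alone. Simulation error is about 0.02–0.03 in HR.

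| Effect of X on recovery (fall in log hazard per SD) | Effect of X on switching (log odds per SD) | No-switch HR | Planned weights | Difference | X added |
|---|---|---|---|---|---|
| 0 | 0 | 1.581 | 1.563 | −0.018 | 1.563 |
| 0 | 0.5 | 1.567 | 1.570 | +0.003 | 1.579 |
| 0 | 1.0 | 1.579 | 1.561 | −0.018 | 1.551 |
| 0.25 | 0 | 1.513 | 1.534 | +0.021 | 1.533 |
| 0.25 | 0.5 | 1.517 | 1.499 | −0.018 | 1.536 |
| 0.25 | 1.0 | 1.553 | 1.480 | −0.073 | 1.520 |
| 0.5 | 0 | 1.455 | 1.465 | +0.010 | 1.466 |
| 0.5 | 0.5 | 1.459 | 1.440 | −0.019 | 1.506 |
| 0.5 | 1.0 | 1.490 | 1.378 | −0.112 | 1.459 |

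Only the two rows with a strong effect on switching and some effect on recovery stand clear of noise.

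**5. Illustration with a hard gate, as Section 6.8 words it.** Assumptions: 400,000 patients, 50–70% of controls passing the gate, 25–42% of at-risk controls switching at day 10, and an oxygenation effect of 0.25–0.5 log hazard per SD. Planned weights gave HR 1.34–1.50 against no-switch values of 1.49–1.56, a bias of about −0.05 to −0.16. Adding the gate to the model brought the estimate within about 0.015 of the truth. With no oxygenation effect on recovery there was no bias.

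**6. At the trial's size.** Assumptions: 82 per arm, 400 trials per scenario, switching at day 10, 38 days of follow-up, truncated weights, and seven noise covariates added to the larger model. About 22–30 controls switch. The RMSE of the log HR, planned against expanded model, was 0.192 vs 0.190, 0.200 vs 0.211, 0.197 vs 0.200 and 0.193 vs 0.182. The sampling SD is about 0.19. The largest bias in step 4 is ln(1.378/1.490) = −0.078, about 0.4 of that SD.

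**The case against.** The case against is substantial, and much of it stands.

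- **The ordinal scale covers most of the rule.** It is the trial's main measure of improvement or worsening, and Section 7.3.1 says the inclusion criteria place every patient in category 4 or 5. A reader might infer that the model ignores the crossover rule altogether. It does not: what is missing is oxygenation within a category, haemoglobin, the group 3 laboratory criteria and the individual decision.
- **Confounding is possible, not shown.** It is tempting to say the adjusted hazard ratio is confounded. The documents give no association between oxygenation and recovery within a category, and haemoglobin may gate switching without confounding.
- **Not everything is available.** One might want all re-eligibility variables as covariates. But Section 7.3.2 does not assess ambient-air SaO2 at category 5 or above, and the Table 1 footnotes and Table 2 list differential counts at baseline. A long list would also overload a model with some 22–30 switchers.
- **Viral load and weight details.** Section 4 says "viral load is measured daily in nasopharyngeal swabs at day 1, 2, 3, 5, 7, 10, 14, 28 or until hospital discharge", so no value is scheduled between days 14 and 28. Carrying the last value forward, stabilising and truncating weights are matters for the SAP and no defect here.
- **The limitation is conceded and the role is supplementary.** True, and it keeps the primary result clear. But the concession concerns confounders that cannot be verified. It does not explain leaving out a measured variable named in the crossover rule.

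**Conclusion.** The point holds in a limited form. Section 10.5.4 closes the switching model at three covariates, while Section 6.8 makes switching depend on oxygenation and haemoglobin as well. Some controls who cannot switch therefore get a positive switching probability, and a plausible, measured confounder is left out. The supplementary switch-adjusted hazard ratios for the primary endpoint, overall survival and time to discharge may stay confounded.

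Under the assumed effects the bias in the primary-endpoint HR is about 0 to −0.16, towards the null because the assumed effect is a benefit. It is zero if oxygenation does not predict recovery given the ordinal score. No figure was worked out for the two secondary endpoints. At about 82 evaluable controls the bias is smaller than the sampling error.

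A reader might infer that the trial's main conclusion is at risk. It is not: the primary log-rank test and hazard ratio ignore switching, and the sample size does not use the IPCW model.

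**What to change.** In Section 10.5.4, and for the same model in Section 10.5.5:

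- Add to patient group, ordinal score and viral load a small set of time-varying oxygenation or severity measures that are collected in every ordinal category, for example FiO2 or PaO2/FiO2 (or oxygen amount) and SOFA. Take the last value before the switch decision.
- Count a control as at risk of switching only from day 10, and only while the Section 6.8 re-eligibility criteria are met, as far as these are recorded. Use haemoglobin, and D-dimer or lymphocytes in group 3, to define that eligibility and not as further covariates.
- Do not use ambient-air SaO2 as a covariate across all patients.

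Before programming the eligibility rule, reconcile the haemoglobin criterion: Section 5.3 asks for at least 10 g/dl, while Section 5.4 excludes values below the lower limit of normal.

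The cost is protocol wording and some programming, with no new data for the suggested covariates. The downside is slightly more variable weights with few switchers, so the change should be justified as reducing bias, not as improving precision.

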#### **10.5.5 Analysis of the Secondary Endpoints**

Overall survival is analyzed by using a Cox regression model adjusting for treatment and patient group, determining hazard ratios with 95% confidence intervals and (descriptive) p-values. Survival estimates are calculated using the Kaplan-Meier method together with 95% log-log-type confidence bands, and the 28-day survival rate will be given for both treatment groups together with 95% confidence intervals. Analogously as for the supplementary analysis of the primary endpoint, an IPCW model and a RPSFT model will additionally be fitted for the secondary endpoint overall survival to assess the potential treatment effect in case patients had not switched from the control to the experimental arm.

Time until discharge will be assessed similarly to the primary endpoint, providing Kaplan-Meier estimates for the cumulative discharge rate for both treatment groups and conducting a log-rank test stratified for the factor “patient group”, and censoring patients who died from any cause at day 84 in analogy to the analysis of the primary endpoint. Analogously as for the sensitivity analysis of the primary endpoint, an IPCW and a RPSFT model will additionally be fitted for the secondary endpoint ‘time until discharge’ to assess the potential treatment effect in case patients had not switched from the control to the experimental arm.

The secondary endpoint “requirement of mechanical ventilation (yes/no)” is analyzed by means of a logistic regression model adjusting for the factors treatment and patient group. Also, absolute and relative frequencies will be given for this endpoint, together with 95% confidence intervals.

The secondary endpoints SARS-CoV-2 viral load and antibody titres will be assessed over time by means of linear mixed models adjusting for treatment group, patient group, and

baseline value as fixed factors, as well as time as repeated factor using an unstructured covariance matrix, calculating least square means estimates and 95% confidence intervals.

While it is indirectly assumed by these models that data will be missing at random, i.e. that the missingness can be explained by observed covariate and outcome values, we will assess the robustness of this assumption by means of sensitivity analyses by means of pattern mixture models assuming that data will be not missing at random.

For all secondary endpoints, the analysis will be conducted based on the FAS and as a sensitivity analysis based on the per protocol population.

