### Inclusion Criteria

1. PCR confirmed SARS-CoV-2 infection in a respiratory tract sample.
2. Oxygen saturation (SaO2) of 94% or less while breathing ambient air or a ratio of the partial pressure of oxygen (PaO2) to the fraction of inspired oxygen (FiO2) of less than 300 mm Hg.
3. High risk due to either

pre-existing or concurrent hematological malignancy and/or active cancer therapy (incl. chemotherapy, radiotherapy, surgery) within the last 24 months or less. (group 1)

and/or

chronic immunosuppression not meeting the criteria of group 1 (group 2)

and/or

Age ≥ 50 - 75 years meeting neither the criteria of group 1 nor group 2 (group 3)  
and at least one of these criteria: Lymphopenia < 0.8 x G/l  
and/or

D-dimer > 1µg/mL

and/or

Age ≥ 75 years meeting neither the criteria of group 1 nor group 2 (group 4)

4. Blood hemoglobin concentration ≥ 10g/dl.
5. Provision of written informed consent.
6. Patient is able to understand and comply with the protocol for the duration of the study, including treatment and scheduled visits and examinations.
7. Male or female patient aged ≥ 18 years.
8. Postmenopausal or evidence of non-childbearing status. For women of childbearing potential: negative urine or serum pregnancy test within 14 days prior to study treatment.

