**Footnotes for schedule of events:**

\*In case of cross-over                      #measured until hospital discharge                      †Once between day 35 and day 84  
( ) Follow-up by regular phone calls                      ‡Blood collection before CP administration

1. **Observation time** for all patients is expected to be at least 3 months after entry into the study. Patients receive convalescent plasma for two days (day 1 and day 2) or standard of care. For patients in the standard arm, cross over is allowed from day 10 in case of not improving or worsening clinical condition. There is a regular *follow-up* of 3 months. All discharged patients are followed by regular phone calls (scheduled days: 14, 17, 21, 24, 28, 32, 42, 49, 56, 70, 84). In person visits after discharge are only advised if clinically indicated. Timing of all visits must be based on the date of first CP administration. The study period ends on the day of the last follow-up visit of the last randomized patient. All Patients with ongoing plasma-related toxicities must be followed until all plasma-related toxicities are resolved.
2. **Informed consent and patient registration:** every patient must sign the informed consent to participate in this trial before starting any trial-related procedures. After signature, a patient ID (three-digit) is generated via registration in the eCRF system. After completion of the screening/baseline visit and assessment of the inclusion and exclusion criteria, **randomisation** is carried out by the responsible investigator **online via <https://randomizer.at>** (Uni Graz) with assignment of the random number.
3. **Demographics:** gender, year of birth, ethnicity
4. **Medical history:** date and type of first symptoms and detailed information on pretreatment including type and composition of prior therapy, family history (cancer, cardiovascular disease, diabetes, rheumatological disease), additional medical history on concomitant diseases in particular cancer and autoimmune diseases and their treatment.
5. **Information on smoking;** duration and amount, pack-years
6. **Signs/symptoms:** infection related and unrelated signs and symptoms, in particular cough, myalgia, fatigue, diarrhoea, vomiting,

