# 1 Introduction

## 1.1 Scientific and Therapeutic Background

The SARS-CoV-2 disease, also known as coronavirus disease 2019 (COVID-19) is a respiratory illness caused by the newly discovered Severe Acute Respiratory Syndrome Coronavirus 2 (SARS-CoV-2). First cases of COVID-19 were reported in December 2019 . The viral infection subsequently rapidly spread worldwide resulting in a pandemic with severe implications on health care systems due to high morbidity and mortality. The infection is characterized by a mild to moderate respiratory illness in most affected patients. However, older people, and patients with concomitant diseases such as chronic respiratory diseases, cardiovascular diseases, cancers, and/or chronic immunosuppression are at high risk to develop severe respiratory distress .

Current control strategies of SARS-CoV-2 disease are limited to prevention, case monitoring and supportive care. A validated vaccine or curative treatment is not available yet, resulting in disease widespread and increasing mortality . Therefore, novel therapeutic options are urgently needed. Outbreaks have overwhelmed the health care systems in several regions of the world, notably in China (Hebei province), Italy (Lombardy) and in France (Alsace). Patients requiring mechanical ventilation were not intubated due to shortages in ventilators, material and staff . Accordingly, early effective treatment is urgently required to avoid the need for mechanical ventilation.

Over the last past decades, convalescent plasma (CP) has been used for the prevention or treatment of various life-threatening infections, especially respiratory viral infections such as H1N1, H5N1 and the coronaviruses SARS1 and MERS . Recently, encouraging results of the treatment of 5 critically ill COVID-19 patients with convalescent plasma have been reported . There are additional non-peer reviewed reports about benefit in SARS-CoV-2 infected patients . SARS-Cov-2 infection is associated with cytokine changes that may partially drive the pathogenesis of Acute Respiratory Distress Syndrome, ARDS . Plasma therapy has a long standing history with an excellent safety profile . From a theoretical perspective, there are *in vitro* concerns whether antibodies against SARS-CoV-2 might lead to Antibody Dependent Enhancement (ADE) of virus entry into cells .

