### **10.5.2 Demographic and other Baseline Characteristics**

Patients’ disposition and reasons for ending the study are presented in frequency distribution tables and individual data listing. Descriptive statistics of the baseline characteristics are generated across all treated patients. Frequency distributions are presented for the categorical variables. Summary statistics and the number of assessed patients are calculated, as appropriate, for the quantitative variables. Individual data is presented in listings.

Categorical baseline characteristics, like sex, concomitant illness at trial initiation, and concomitant treatment maintained, is summarized by frequency tables. Summary statistics such as mean, standard deviation, median, first and third, quartile, as well as minimum and maximum, are provided for quantitative variables like age, weight, laboratory values.

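### The overall-survival Cox model leaves out age, which is collected and is open-ended in groups 1 and 2; adding it would bring a small gain in power and conditional accuracy, with no change to validity

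*Protocol*

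**What the plan says.** Section 10.5.5 states the survival model with its covariates: "Overall survival is analyzed by using a Cox regression model adjusting for treatment and patient group". The p-values from this model are described there as descriptive only. The need for mechanical ventilation "is analyzed by means of a logistic regression model adjusting for the factors treatment and patient group". Neither model has an age term. Section 6.6 stratifies randomisation by the four risk groups only, so age is not balanced within a group.

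Age is available. Footnote 3 of the trial schedule lists demographics as "gender, year of birth, ethnicity", and section 10.5.2 says that summary statistics "are provided for quantitative variables like age, weight, laboratory values". The protocol also treats age as prognostic: section 1.1 places "older people, and patients with concomitant diseases such as chronic respiratory diseases" and others at high risk of severe respiratory distress.

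Groups 3 and 4 are age bands (50 to 75, and 75 and over), so the group factor carries part of the age effect. Groups 1 and 2 are not. Group 2 is "chronic immunosuppression not meeting the criteria of group 1 (group 2"), group 1 is defined by malignancy or cancer therapy, and the only age limit for either is "Male or female patient aged ≥ 18 years". The synopsis expects 25% of participants in each group, so these two make up half the trial.

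**The concern.** Within groups 1 and 2 a patient of 25 and one of 85 enter the model at the same baseline risk. If age is strongly prognostic, this has two consequences. The log hazard ratio moves with whatever age difference chance leaves between the arms, and some power is given up. Section 10.3 expects a gain in power from adjusting for patient group, and the same reasoning extends to age, which needs no new data. There is also a practical side. The trial is open label and its baseline table will show any age difference. Without a planned age term, a visible imbalance can be handled only by an adjustment chosen after the data are seen.

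**Working it through.** **The plan's own figures.**
- Primary endpoint (two-sided 5%, 80% power, HR 1.6): the Schoenfeld formula gives 142.1 events (stated 142). The mean event probability at day 38 is (0.807 + 0.928)/2 = 0.868, so N = 142.1/0.868 = 163.8 (stated 164). Then 164/0.95 = 172.6, rounded up to 173 and made even, 174 as stated.
- Overall survival: 20% and 13% mortality give ln(0.80)/ln(0.87) = 1.602 (stated 1.6). As an HR for plasma versus standard this is 1/1.6 = 0.625.

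**How many deaths.** No number of deaths or power is stated for overall survival. Section 10.3 gives 20% control mortality once without a time point and once as a 38-day rate, so two readings are possible.
- 20% versus 13% by the end of follow-up: 87 × 0.20 + 87 × 0.13 = 28.7 deaths in 174 patients, Schoenfeld power 24%. In 164 patients it is 27.1 deaths, power 23%.
- 20% versus 13% by day 38, with a constant hazard to day 84: 1 − 0.80^(84/38) = 0.389 and 1 − 0.87^(84/38) = 0.265. That is 82 × (0.389 + 0.265) = about 54 deaths in 164 patients, power 41%, or about 57 in 174.

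**Effect of adding age.** The protocol gives neither an age effect nor an age spread, so both are assumptions. One simulation used 2,000 trials per setting, 164 patients (groups 42/40/42/40), 1:1 allocation within group, exponential survival with 20% control mortality at day 38 and HR 1.6. Age SD in groups 1 and 2 was 10 or 15 years. Power without and with age:

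| Age SD | Follow-up (deaths) | HR 1.3 per decade | HR 1.5 | HR 2.0 |
|---|---|---|---|---|
| 15 | 38 days (about 27) | 21.1 → 21.2% | 20.4 → 20.6% | 18.1 → 20.9% |
| 15 | 84 days (51 to 53) | 37.9 → 39.0% | 35.5 → 38.4% | 32.9 → 37.0% |
| 10 | 84 days (51 to 53) | not run | 38.4 → 38.8% | 35.2 → 38.9% |

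The Monte Carlo standard error of each figure is about 1 point. Widening the age effect to 1.3 to 2.5 per decade gives gains of about 0 to 2 points with 29 deaths and about 1 to 8 points with 52 to 57 deaths.

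**Where the gain comes from.** At 2.0 per decade, SD 15 and 84 days, the median log HR goes from −0.440 to −0.482 and the standard error from 0.288 to 0.292. The ratios are 0.440/0.288 = 1.53 and 0.482/0.292 = 1.65. The adjusted hazard ratio lies slightly further from 1, and precision does not improve.

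**Validity.** With no treatment effect, rejection was 5.3% without and 5.7% with age (1.5 per decade), and 5.1% and 5.0% (2.0 per decade).

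**Chance imbalance.** The between-arm difference in mean age has an SD of 1.3 to 1.8 years. Each year moves the log HR by 0.03 to 0.06 without age and by about 0.00 to 0.01 with it. The two estimates differ with an SD of 0.055 to 0.145 in log HR (exp gives about 6% to 16%), against a standard error of 0.28 to 0.40.

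**Overall error.** With about 29 deaths, the root-mean-square error of the log HR around ln(0.625), without and with age, was 0.403 and 0.407 (1.3 per decade), 0.403 and 0.409 (1.7), 0.405 and 0.413 (2.0), and 0.396 and 0.411 (2.5). Age brings no improvement here.

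**The case against.** The case for leaving the model alone is strong. Adjusting for the stratification factor is standard. Randomisation protects the test, and over all simulated trials the unadjusted hazard ratio averages 0.61 to 0.63 against a true 0.625. The p-value is descriptive and power is low either way. Age effect and spread are assumed, other baseline factors such as ordinal category 4 versus 5 could also be argued for, and an unseen SAP may add an adjusted sensitivity analysis. All of this stands as a limit on weight. It does not remove the point, because section 10.5.5 itself states the covariate set and age is the one collected factor that the protocol both names as a risk and uses to define two groups.

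Two stronger readings are tempting. A reader might infer that the planned hazard ratio is biased, or that adjusting brings it closer to the truth. In the sixth of trials where the plasma arm is oldest, the estimate is 0.69, 0.71 and 0.69 without age (1.7, 2.0 and 2.5 per decade) and 0.63, 0.61 and 0.60 with it. But that is one tail. In the opposite sixth the unadjusted estimate errs the other way (0.57, 0.54 and 0.55). Even in the first tail, ln(0.69) − ln(0.63) = 0.09 is about a quarter of a standard error of 0.39, and the unadjusted 95% interval covered 0.625 in 93 to 96% of trials. A reader might also extend the figures to the ventilation model, but the gain there was not quantified.

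**Conclusion.** The point holds as a minor improvement to a secondary analysis. The planned survival analysis is valid and unbiased on average, and its interval allows for chance imbalance. Adding age would buy about 0 to 2 points of power if 20% control mortality is reached at day 84, or about 1 to 8 points if it is reached at day 38. It would also make the hazard ratio practically independent of a chance age difference between arms. It would not make the estimate more accurate overall. These sizes rest on assumed age effects of HR 1.3 to 2.5 per decade, an assumed age spread in groups 1 and 2, exponential survival and the protocol's survival HR of 1.6. At the weak end of the age effect the benefit is close to nil. The primary test and the sample size are untouched.

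**What to change.** In section 10.5.5, add age (continuous, derived from year of birth) to the Cox model for overall survival, next to treatment and patient group, and fix this before any outcome data by arm are reviewed. The same term in the logistic model for ventilation is optional.

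The cost is one more parameter and a very slightly larger standard error (for example 0.292 instead of 0.288). No new data are needed, since year of birth is already recorded at baseline, and the SAP is due only before database lock (section 10.5.1).
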